#### Mandatory notification of radiographic 'red flags'

In the event of any radiographic red flags (including suspected malignancy, unresolved fracture, infection) reported by the Consultant Radiologist a standard fax will be sent with a copy of the x-ray report to the General Practice notifying them of this. This will subsequently be confirmed by letter.

#### Discretionary notification of other significant radiographic abnormality

At the discretion of the Consultant Rheumatologist, the General Practice will be notified of other significant radiographic abnormality (e.g. previous fracture, inflammatory arthropathy).

#### Availability of x-ray report on request

To prevent unnecessary duplication of x-rays, participants' GPs can request an x-ray report if they feel it would be valuable for clinical management.

#### Quality assurance and control

Quality assurance and control are important for the integrity of longitudinal studies and the validity of their conclusions [69]. This is especially true of observer-dependent methods of data-gathering. In the clinical assessment phase of the study, the clinical interview and physical assessment, ultrasound, digital images, plantar pressure and the taking and scoring of x-ray will be subject to a number of quality control procedures.

Inter- and intra-assessor reliability of foot interview and examination variables have been established, where possible, from the published literature [49-54,70]. Assessors will undergo training in consent procedures, clinical interview and physical assessment techniques. All Research Assessors will be required to conduct at least two clinical assessments prior to the commencement of data collection. During the first month clinics with reduced numbers of participants will be held to allow all study procedures to be tested and reviewed. All radiographers participating in the study will also receive training prior to the commencement of the study.

Selected Research Assessors will receive ultrasound training on a formally assessed course, Focused Specialist Ultrasound Practice, run by University of Derby (UK). This course consists of the principles of ultrasound physics and imaging science. The Research Assessors will then receive specific clinical training from a Consultant Musculoskeletal Sonographer to assess the plantar fascia thickness. In addition to meeting the course assessment requirements clinical competence for the study will be assessed by the Consultant Sonographer following a period of supervision and mentorship.

The Research Radiographer will be trained in the methods for scoring the plain radiographs. This single observer will score all images and intra-observer variability will be assessed using 60 sets of images scored eight weeks apart. Inter-observer variability will be assessed using a second observer with prior experience of grading foot x-rays for OA who will also grade 60 sets of images.

A detailed Assessor Manual with protocols for obtaining written informed consent, digital photography, clinical interview and physical assessment, administration of the self-complete questionnaire, anthropometric measurement, plain radiography, and ultrasound will be provided to all members of the study team for reference during the entire study period.

During the data collection period, digital photographs for all participants will be reviewed and participants with any missing or spoilt images will be recalled to repeat the photographs. Quality control sessions for consent procedures, clinical interview and physical assessment, radiography and ultrasound will be undertaken at regular intervals throughout the study. These sessions will include observation of assessments in clinic by the Principal Investigator, structured observation of assessments in a healthy volunteer, and direct inter-assessor comparisons on selected participants. Observation of radiography and ultrasound will be undertaken by the Research Radiographer and Consultant Musculoskeletal Sonographer respectively. The outcome of each quality control session will be fed back to the individual Research Assessor and the group as a whole.

### Phase 3: Review of general practice medical records

All participants in Phase 1 who give permission for their GP records to be accessed will have their computerised medical records tagged by a member of the Research Centre's Health Informatics Specialist team. All consultations for the 18-month period prior to clinic attendance, and for the three-year period following clinic attendance, will be identified. The four practices participating in this study are fully computerised and undergo annual audits completed by the Health Informatics team to assess the quality and completeness of the data entry at the practices [71].

This data will cover consultations, prescriptions, and referrals. All relevant foot-related consultations will be identified using search techniques based on Read codes and free text entries, which have been previously developed and successfully applied by the Research Centre [28,72]. Participants with a relevant recorded consultation will be classified into those receiving an OA diagnosis recorded by their GP and those receiving non-specific symptom codes (e.g. arthralgia). In addition, all comorbid consultations will be identified and sub-grouped by Read code chapter.

Patterns of primary and secondary health care utilisation will be compared between Phase 2 participants and Phase 1 participants who did not attend the research clinic. All sensitive data (name, contact details) will be removed from the medical records data and the consultation data will be linked to the survey and clinical assessment data by unique survey identifier.

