Pre-defined protocols for all components of the interview and assessment will be used for standardisation between Research Assessors. Assessment findings will be recorded on a standard form that is to be checked for missing data immediately post-assessment by the Clinic Co-ordinator or Clinic Support Worker. Discussion between Research Assessors and participants about diagnosis and/or appropriate management will be discouraged. Participants will be advised to discuss clinical queries with their General Practitioner. The interview and assessment will take approximately 40 minutes to complete for each participant.

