#### Mandatory notification of clinical 'red flags'

All participants will be routinely screened during the clinical assessment for signs and symptoms suggesting potentially serious pathology requiring urgent medical attention (Table 2). These are: recent trauma to the feet or hands that may have resulted in significant tissue damage; recent sudden worsening of foot or hand symptoms; and acutely hot, swollen, painful feet or hands [68]. In the event of such findings, participants will be informed that they require urgent attention, a standard fax will be immediately sent to the General Practice, and appropriate medical attention arranged the same day. A letter of confirmation will be subsequently sent to the participants' General Practice.

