#### Describing self-care and primary care

Annual consultation rates and cumulative consultation probabilities will be calculated over the three-year period. Using logistic regression and survival analysis techniques, we will investigate further how different phenotypes relate to subsequent patterns of primary care consultation (for joint pain, other morbidities, and specifically for OA) and referral to secondary care. Self-care reported by participants in the surveys at each 18 month time-point will be described.

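### Consultations are counted from the clinic visit, but the visit itself prompts some contacts in attenders only, and nothing in the plan separates them

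*Protocol article*

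**What the plan says.** Under *Phase 3: Review of general practice medical records* the window is fixed as follows: "All consultations for the 18-month period prior to clinic attendance, and for the three-year period following clinic attendance, will be identified". Foot-related contacts are then selected by Read code and free text. The same section plans a comparison of clinic attenders with non-attenders: "Patterns of primary and secondary health care utilisation will be compared between Phase 2 participants and Phase 1 participants who did not attend the research" […].

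Under *Describing self-care and primary care*: "Annual consultation rates and cumulative consultation probabilities will be calculated over the three-year period". Logistic regression and survival methods then relate phenotype to later consultation and referral. *The presentation and diagnosis of OA in primary care* models who consults.

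The clinic visit that opens the window also sets contacts in motion:

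- For clinical red flags, "a standard fax will be immediately sent to the General Practice, and appropriate medical attention arranged the same day". The triggers include "recent sudden worsening of foot or hand symptoms; and acutely hot, swollen, painful feet or hands".
- Under *Clinical interview and physical examination*, "Participants will be advised to discuss clinical queries with their General Practitioner".
- For radiographic red flags, "a standard fax will be sent with a copy of the x-ray report to the General Practice notifying them of this".

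The article does not say that contacts arising in these ways are flagged, excluded or analysed separately.

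**The concern.** Time zero for the consultation outcomes is a study event that can itself cause the outcome. A participant with an acutely swollen foot is seen that day because the clinic arranged it. Another asks the assessor about a deformity, is directed to the GP, and goes. Either may have no other foot contact in three years, yet each counts as a consulter with an early event.

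Two features make this a bias rather than noise. It can only add events, and it adds them only among attenders, mostly soon after the visit. It also depends on symptoms: acute presentations and people with questions are the ones sent. Associations between phenotype and consultation can therefore be shifted upward for the phenotypes that trigger a red flag or a query.

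At stake are the consultation results for aims (iv) and (v) and the attender comparison. In *Modelling the outcomes of care*, the propensity score is described as a person's likelihood of seeking care given their characteristics. A contact arranged by the research clinic does not measure that.

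**Working it through.** **Step 1. Does the rule, as written, take these contacts in?**

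- Start of the window: clinic attendance. A same-day contact falls inside it.
- Filter: foot-related by code or free text. A red-flag contact about a foot passes. One about a hand need not.
- Source: GP records, covering consultations, prescriptions and referrals. A query taken to the GP is recorded there. Same-day attention may be a GP contact or a hospital one, and both primary and secondary care use are compared.
- Separation: none stated.

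**Step 2. Inputs for the size.** The article gives no rate of red flags or prompted visits and no expected consultation rate for this cohort, so there is no plan figure to reproduce. The inputs are:

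- Background three-year consultation probability of about 20%. *Background* says about 80% of people with musculoskeletal foot problems do not appear to consult over three years. This is not the 20% in *Sample size*, which is the risk of poor functional outcome.
- Phase 2 target of 506 (*Sample size*: 426 + 80 = 506).
- s = the share, among attenders who would not otherwise consult in three years, whose only foot contact is study-prompted. This is an assumption; 1%, 3% and 5% are shown.

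**Step 3. Formulas.**

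- Three-year proportion = 0.20 + 0.80 × s.
- Year-1 background under a constant hazard = 1 − 0.80^(1/3) = 0.0717.
- Year-1 proportion, with all prompted contacts falling in year 1 = 0.0717 + 0.80 × s.
- Extra consulters = 506 × 0.80 × s.

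**Step 4. Results.**

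| s (assumed) | Three-year proportion | Relative rise | Year-1 probability | Relative rise | Extra consulters |
|---|---|---|---|---|---|
| 0 | 20.0% | – | 7.2% | – | 0 |
| 1% | 20.8% | 4% | 8.0% | 11% | about 4 |
| 3% | 22.4% | 12% | 9.6% | 33% | about 12 |
| 5% | 24.0% | 20% | 11.2% | 56% | about 20 |

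The relative effect is larger in year 1 because the added events fall early against a smaller base.

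**The case against.** **The quoted sentence is an extraction window, not a scoring rule, and event definitions often sit in a fuller document.** This is partly right. The full protocol or analysis plan is not shown and may separate these contacts. But the article itself fixes the start at clinic attendance, computes rates over the whole period and commits to the attender comparison. Applied as written, that includes the prompted contacts.

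**The design already limits the number.** Discussion of diagnosis and management is discouraged, findings are fed back only in specific circumstances, and red flags are a short list of acute presentations that also covers hands. This stands as a reason to expect a small effect. It does not separate the contacts that do occur. The 18 months of records before clinic are unaffected and give a useful contrast.

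**Use on advice is still use.** This stands. A reader might infer that aims (iv) and (v) concern only people who present of their own accord. The aims are not worded that way; only the description of the propensity score refers to care-seeking.

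**The two comparison groups differ anyway.** This also stands. A reader might turn the table into a false attender versus non-attender ratio of 1.04 to 1.20. That presumes equal true rates, yet attenders are selected for foot pain in the past twelve months and non-attenders include people without it. Prompted contacts add to whatever difference exists; the ratio itself is not supported.

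**Conclusion.** The point holds as an unseparated source of upward bias in the consultation outcomes of attenders, strongest just after the visit. Its size cannot be derived from the document. The figures above rest on an assumed s, a 20% background taken from the article's introduction, a constant hazard, and all prompted contacts falling in year 1. At s = 1% the excess is about four people in 506.

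Two stronger inferences should be resisted. A reader might apply s to everyone who has not consulted by the end of year 1 (92.8%) and obtain 8.1%, 10.0% and 11.8%. Those figures also give prompted contacts to people who would consult in years 2 and 3 anyway, which is outside the definition of s used here. A reader might also conclude that prompted contacts should be removed from every analysis. For *Modelling the outcomes of care* that would class people who received care as untreated.

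The primary aim in *Sample size*, functional outcome at three years by radiographic OA, is not affected. The change is still worth making because it is cheap and is best fixed before the records are analysed.

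**What to change.** In *Phase 3* and *Describing self-care and primary care*, state that:

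1. Contacts arranged under the red-flag procedure are flagged from the faxes and confirmation letters the study already sends. They do not count as consultation or referral events in the care-seeking analyses: who consults, rates and cumulative probabilities, and the attender comparison.
2. The all-contacts count is reported alongside.
3. A prespecified sensitivity analysis for attenders omits a short fixed period after clinic. The document does not determine its length; four weeks is one example. This is the only handle on visits prompted by advice, since no log of that advice is described, and later advised visits will still be missed. It should not be the main analysis: non-attenders have no clinic date to start it from, and it drops genuine consultations.
4. In *Modelling the outcomes of care*, flagged contacts stay in the care exposure, because care was received, but are not treated as care-seeking in the propensity model.

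The notification and advice procedures stay as they are. The cost is a little extra record flagging, and the loss of a few genuine early consultations from the sensitivity analysis only.

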## Methods

### Study design

The study is a three-year population-based prospective observational cohort study. Ethical approval for all phases of the study has been obtained from Coventry Research Ethics Committee (REC reference number: 10/H1210/5). Adults aged 50 years and over registered with four separate local general practices will be invited to participate in the study, irrespective of consultation (Figure 1). Data collection will be in five phases:

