### Phase 1: Baseline postal Health Survey questionnaire

All adults aged 50 years and over registered with four local general practices (mailed population approximately 9000 adults) will be mailed a letter of invitation from their general practitioner, a Participant Information Sheet, a Health Survey questionnaire, and a pre-paid return envelope. The lead general practitioner (GP) at each practice will be invited to identify potentially vulnerable patients (e.g. dementia, severe or terminal illnesses) they feel should be excluded from the study. Practice lists will be screened prior to mailing to ensure that addresses are up to date and exclude any recent deaths or departures from the practice list. Health Survey questionnaires will be mailed in batches (n = 500) to ensure regular recruitment to research clinics (Phase 2) and to limit the interval between questionnaire completion and clinic attendance. Pilot cognitive interviews have been undertaken with members of the Research Centre's Research User Group to test the Health Survey questionnaire's layout, readability, content, language and length. The questionnaire will be divided into five main sections: (i) general health (including generic measures of physical function, psychosocial factors and lifestyle [32-36] (Additional File 1: Appendix 1)); (ii) specific health problems including musculoskeletal co-morbidity and pain [37,38]; (iii) questions concerning the presence [39], duration, location [14], severity [40], and impact [41,42] of foot pain; (iv) demographic and socioeconomic characteristics [43,44]; and (v) employment (Table 1). Non-responders to the questionnaire will be sent a reminder postcard after two weeks. Those who do not respond to the reminder postcard will be sent a repeat questionnaire and Participant Information Sheet with a further covering letter four weeks after the initial mailing. Questionnaires will ask for consent (i) to contact participants again by post and/or (ii) to review medical records. Responders will be given the option of providing their telephone number for further contact.

**Table 1 T1:** Content of baseline postal Health Survey questionnaire

Concept	Measurement method	Detail

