### Phase 2: Baseline Clinical Assessment Study of the Foot (CASF)

Responders to the Health Survey questionnaire who report experiencing pain in or around the foot within the last twelve months and who provide written consent to further contact will be sent a letter of invitation to attend a research clinic. The letter of invitation will be accompanied by a Participant Information Sheet providing details of the study. Participants will be asked to telephone the Research Centre if they are interested in taking part in order to book an appointment. Non-responders to this initial invitation letter will be sent a reminder invitation approximately two weeks later.

Those willing to take part in the study will be booked into the next convenient appointment and, if necessary, travel arrangements (taxi) made. Postal confirmation of the appointment will be made by letter and then by a reminder postcard shortly prior to the appointment. The postcard will be mailed in an envelope to maintain confidentiality about the nature of the appointment. Participants who do not attend the clinic for their specified appointment will be sent another letter asking them to re-contact the Research Centre and book another appointment if they still wish to participate.

Assessment clinics for the study will be conducted twice-weekly in a local NHS Trust community rheumatology hospital. A maximum of 12 appointments per week are scheduled. Each clinic is to be staffed by a Clinic Co-ordinator, a Clinic Support Worker, two trained Health Professionals (podiatrist or physiotherapist) acting as Research Assessors, one trained Research Assessor (physiotherapist, radiographer or nurse) acting as an Ultrasonographer, and two Radiographers.

On arriving at clinic, participants will be issued with a file containing all assessment documentation marked with their unique study number. Prior to commencing the assessment, the procedures outlined in the Participant Information Sheet will be discussed with each participant. Participants will be given the opportunity to ask questions. Written informed consent to take part in the study will be obtained from all participants. Appropriate clothing (shorts) for the assessment will be provided.

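### The record-review window is tied to clinic attendance, so it cannot be applied to the non-attenders in the planned health-care-use comparison, and that comparator is not separated by foot pain

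*Protocol article*

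**What the plan says.** All the statements are in the protocol article.

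- **Whose records are reviewed** (Phase 3): "All participants in Phase 1 who give permission for their GP records to be accessed will have their computerised medical records tagged".
- **Over what period** (Phase 3): "All consultations for the 18-month period prior to clinic attendance, and for the three-year period following clinic attendance, will be identified". No other index date is given for the record review.
- **What is compared** (Phase 3): the section states that "utilisation will be compared between Phase 2 participants and Phase 1 participants who did not attend the research clinic".
- **Who can be a Phase 2 participant** (Phase 2): survey responders "who report experiencing pain in or around the foot within the last twelve months and who provide written consent to further contact".
- **Who can be a Phase 1 participant** (Study design): adults aged 50 and over "registered with four separate local general practices will be invited to participate in the study, irrespective of consultation", from a "mailed population approximately 9000 adults" (Phase 1). Foot pain is not required.

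Two further points bear on the remedy. The Phase 5 section times the three-year survey from the baseline Health Survey, a date that every Phase 1 participant has. Table 1 shows that the baseline survey asks everyone about foot pain in the last year.

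**The concern.** Two features of the planned comparison conflict with the rest of the plan.

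First, the window starts and ends relative to an event that the comparison group, by definition, did not have. Whoever runs the extraction must supply a date for non-attenders. If non-attenders receive an improvised date, such as the mailing or survey return, while attenders keep the clinic date, the two groups run on different clocks. Attenders must also remain registered, accept the invitation and book before their clock starts. Non-attenders would face no such condition.

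Second, every attender reported foot pain, whereas non-attenders are taken as one undivided group. As written, that group pools respondents without foot pain, respondents with foot pain who did not agree to further contact, and respondents with foot pain who were invited but did not come. Foot-related consultations are a main item extracted from the records, and one would expect them to be more frequent in people with foot pain. A reader could not tell whether a higher figure in attenders reflects who attends or simply who has sore feet. The result could not show whether clinic attenders resemble other people with foot pain in their use of care, which is a natural use for such a comparison.

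**Working it through.** **1. Can the window be applied?** Set the three Phase 3 statements side by side.

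| Element | Attenders | Non-attenders |
|---|---|---|
| Records reviewed | yes, with permission | yes, with permission |
| Clinic date | exists | does not exist |
| Start (clinic date minus 18 months) | defined | undefined |
| End (clinic date plus 3 years) | defined | undefined |

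The rule fails for the whole comparison group. This measures the gap in the definition, not a bias. The bias from unequal clocks cannot be calculated, because the length of the survey-to-clinic interval is not stated. The Phase 1 section says only that batch mailing is meant to limit it.

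**2. The plan's own figures.** There is none for this comparison. The Sample size section sizes the radiographic OA contrast: 20% versus 0.20 × 1.62 = 32.4%, 80% power and 5% two-sided (sidedness assumed). With a continuity correction this gives 213 per group, or 426, and 426 + 80 = 506, as stated. Only the 506 is used below, as the planned number of attenders.

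**3. How much of the comparator has no foot pain?** Let R be the number of survey responders and p the proportion reporting foot pain. The document gives neither, so both are assumed. The share of non-attenders without foot pain is

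(1 − p) × R / (R − 506).

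For response of 40% to 80% of 9000 (R = 3600 to 7200):

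| p | Share without foot pain |
|---|---|
| 20% | 86–93% |
| 30% | 75–81% |
| 50% | 54–58% |
| 60% | 43–47% |

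The share passes one half when p is below 0.5 + 253/R, that is, below about 53% to 57%.

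**4. How large a contrast can foot-pain status alone produce?** Suppose attendance makes no difference among people with foot pain.

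*Route A, three-year consultation probabilities.* The Background says about 80% of people with musculoskeletal foot problems do not consult over three years, so take 20% who do. Let q be the assumed share of non-attenders with foot pain and b the assumed probability in people without it. The pooled non-attender probability is 0.20q + b(1 − q), and the apparent ratio is 0.20 divided by that.

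| b | q = 0.15 | q = 0.40 |
|---|---|---|
| 1% | 0.20/0.0385 = 5.2 | 0.20/0.086 = 2.3 |
| 5% | 0.20/0.0725 = 2.8 | 0.20/0.11 = 1.8 |
| 10% | 0.20/0.115 = 1.7 | 0.20/0.14 = 1.4 |

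*Route B, rate ratios.* Let r be the assumed ratio of foot-related consultation rates with and without foot pain, and s the share from step 3 at 60% response (R = 5400). The apparent ratio is r / [s + (1 − s)r].

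| r | p = 20% | p = 30% | p = 50% |
|---|---|---|---|
| 2 | 1.79 | 1.63 | 1.38 |
| 3 | 2.43 | 2.06 | 1.58 |
| 5 | 3.40 | 2.62 | 1.79 |

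For example, with r = 3 and p = 30%: s = 3780/4894 = 0.772, and 3/(0.772 + 0.228 × 3) = 2.06.

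Together the two routes span about 1.4 to 5. The direction is fixed as long as people with foot pain consult more often for their feet. The size is not.

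**The case against.** The strongest reply is that this is one missing clause in a condensed article. Records are computerised and tagged for every consenting participant, the survey date exists for all, and foot-pain status is collected and can be linked, so nothing is lost by settling the details at extraction. The comparison is worded descriptively and does not appear in the aims, the sample size or the statistical analysis sections. Higher use of care among people with foot pain is a real difference between the groups, not an artefact.

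Much of this stands. It limits the severity and rules out several readings that a reader might infer:

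- *That no valid window is possible.* None is defined for non-attenders, but the Phase 5 section already uses a date that would serve.
- *That non-attenders mostly lack foot pain.* The document gives neither a response rate nor a prevalence. This holds only below a prevalence of about 53% to 57%, under the assumed response range.
- *That the excess is 2.3- to 5.2-fold.* Those values need a 1% consultation probability in people without foot pain, which has no source. At 5% to 10% the range is about 1.4 to 2.8. The 20% also describes people with musculoskeletal foot problems, not everyone with any foot pain in the past year. The calculation covers foot-related consultation only, whereas the planned comparison covers health-care use more widely.
- *That the plan claims an effect of attendance.* It does not.

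The appeal to condensation does not stand. The article does not leave the window and comparator open. It names both, and they are incompatible as written.

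**Conclusion.** The point holds, at moderate severity. The stated window cannot be applied to the stated comparison group, and the comparator mixes foot-pain status with attendance. The first conclusion needs no assumption, because it follows from the Phase 3 text alone. The second follows from the Phase 2 entry criteria. Its numerical size, roughly 1.4- to 5-fold for foot-related consultation, is an illustration that rests on assumed prevalence, response and consultation rates. It should not be quoted as an estimate. Analyses confined to Phase 2 participants and the 426/506 sample size are unaffected.

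**What to change.** For this comparison only:

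1. Index every Phase 1 participant, attender or not, on the baseline Health Survey date, and take records from 18 months before to three years after it.
2. Start the follow-up part at the same fixed landmark after the survey in both groups, among people still alive and registered then. Indexing on the survey date alone is not enough: attenders must by definition still be present at their clinic visit, so the survey-to-clinic interval would be guaranteed time in their follow-up but not in that of non-attenders. Set the landmark in advance, and classify people by whether they have attended by then.
3. Make the main contrast Phase 2 participants versus respondents who reported foot pain but did not attend. Show respondents without foot pain as a separate group.
4. Keep the clinic-date window for analyses confined to Phase 2.

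The cost is small: a changed extraction request, a slightly wider record pull for attenders, and the loss of the few participants who leave before the landmark. No new participants or data items are needed. The change should be made before extraction.
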